#### 2.2.4. Recruitment

For the intervention study, fathers and their primary school-aged children (6–8 years old) will be recruited in multiple ways through convenience sampling and snowball sampling. These methods of sampling will be used in order to reach a sufficient number of male participants, as research has indicated that it is difficult to engage fathers for lifestyle interventions [12,53]. More specifically, researchers will recruit fathers through contacting their acquaintances, friends and family. Fathers will also be recruited online, through social media and e-mail. Last, flyers and posters will be distributed in schools, sports clubs, libraries, etc. Additionally, snowball sampling will be used where registered fathers will be asked to contact their friends, family or acquaintances and invite them to participate in the intervention. The recruitment procedures will continue until the required number of participants is reached.

#### 2.2.5. Study Design and Randomization

The Run Daddy Run intervention will be evaluated through a quasi-experimental study, with a non-equivalent pre-test post-test control group design in which participants will not be randomly assigned to the control group (CG) or intervention group (IG), but will be recruited subsequently (i.e., first the CG, then the IG—see Figure 4 for a visual representation of the study design and flow). This will be done for convenience reasons and because the study load between the two groups will differ significantly, thus correctly and transparently communicating to the participants what is expected is important for an optimal sample size and to minimize drop-out. The IG will receive the Run Daddy Run intervention, whereas the CG will receive a report of the data acquired with the online questionnaire (i.e., report with information on BMI, PA levels, etc.) after the intervention took place (in June 2020). At that moment, the CG will also get access to all the intervention materials and documents used in the intervention. Measurements will be taken before (i.e., baseline) and after the intervention (i.e., post-test) for both the IG and CG. Additionally, a follow-up measurement will be conducted five months after the intervention.

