#### 2.2.3. Sample Size

Using the software GPower 3.0.10 (Universität Kiel, Kiel, Germany) [52], the required sample size was calculated. Based on the obtained effect sizes of previously implemented interventions for fathers and children targeting co-PA [52], a minimally detectable effect size of f = 0.20 was intended for the main PA outcome (i.e., co-PA) in the present study. This effect size was slightly more conservative than the obtained effect sizes for co-PA in the studies of Morgan et al. (i.e., n = 6 reported effect sizes across 3 studies, range f = 0.42–0.73, mean f = 0.58). This sample size calculation was based on 80% power to detect a significant difference in PA outcomes between groups, significance level alpha 0.05, having two groups (intervention and control group) and three measurements (pre-test, post-test and follow-up). The a priori power analysis suggested a total sample size of 42 families (fathers and children). Assuming an attrition rate of 20% [10], a total sample size of 51 fathers will be required.

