#### 2.2.6. Procedure

The recruitment phase will take place in November 2019–January 2020. The CG will be asked to participate in a study that investigates health-related behaviors over time, whereas the IG will be asked to participate in a study providing six (inter)active father-child sessions over a total period of 14 weeks. When interested in participating, fathers will be able to register for the study by contacting the researcher (control group) or by registering through an online registration form available on the Run Daddy Run website (intervention group). After registration, the participants will be checked for their eligibility (see Section 2.2.2) and eligible fathers will be asked to complete an online questionnaire and to wear an accelerometer during 7 consecutive days (see Section 2.2.7). The baseline measurements will take place in November-December 2019 for the CG and in January 2019 for the IG. After the completion of the baseline measurements, participants of the IG will receive an email or text message in which they will be informed about the start of the intervention (i.e., date, time and location) and some practical information regarding the first session. In each session, attendance of the father-child dyads will be logged by the facilitators. When a father-child dyad does not attend a certain session, a message (i.e., text message or email) will be sent afterwards with a link to the website where both the information given in the information part and the exercises in the practical part can be found. However, participants who do not attend the first two sessions, will be excluded from the study. Last, post-test measurements will take place after the intervention, in June 2020 and the follow-up measurements will take place in November 2020.

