#### 2.2.8. Data Analysis

Descriptive statistics will be provided for the sample characteristics, i.e., for the total sample and by study group (i.e., CG and IG). To evaluate the intervention effect (i.e., the difference in pre-post-follow up evolution between control and intervention group), multilevel analyses will be used to take into account the clustering of measurements within participants. Time by group interaction terms will be reported. Age and gender will be considered as confounders in the analyses. For comparison with previous research [10,28], Cohen’s *d* will be reported, which is the difference of two group means divided by the standard deviation from the data. For the process evaluation, the six key elements described in Section 2.2.9 will be quantitatively and qualitatively analyzed. All statistical analyses will be performed using the statistical program SPSS 26.0 for Windows [77].

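### The control group gets its report and all intervention materials in June 2020, so the November 2020 follow-up compares the programme with a control group that has had the materials

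*Protocol article*

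**What the plan says.** Section 2.2.5 (Study Design and Randomization) describes what the CG receives and when: a summary of its own questionnaire data ("i.e., report with information on BMI, PA levels, etc.) after the intervention took place (in June 2020"), and then "At that moment, the CG will also get access to all the intervention materials and documents used in the intervention".

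The same section continues: "Additionally, a follow-up measurement will be conducted five months after the intervention". Section 2.2.6 (Procedure) supplies the dates: "post-test measurements will take place after the intervention, in June 2020 and the follow-up measurements will take place in November 2020".

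Section 2.2.8 (Data Analysis) defines the intervention effect as "the difference in pre-post-follow up evolution between control and intervention group" and adds: "Time by group interaction terms will be reported". Section 2.2.3 (Sample Size) is built on the same structure: "having two groups (intervention and control group) and three measurements (pre-test, post-test and follow-up". November is therefore part of the declared between-group effect on the primary outcome.

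Section 2.2.7 says that follow-up uses the questionnaire only, without accelerometry. The limitations in Section 4 do not mention the June release.

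**The concern.** A between-group follow-up comparison needs the comparator to stay what it was until the last measurement. Here it changes about five months earlier. The CG receives feedback that covers physical activity, the target behaviour, together with the programme's materials. Sections 2.2.1 and 2.2.6 treat such content as active: activity ideas with instructions are listed among the website's behaviour-change techniques, and IG families who miss a session are directed to the session information and exercises online.

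If CG families use what they are given, their co-physical activity may rise between June and November. The November group difference would then shrink even if the IG had kept all of its gain. A small November difference would have two explanations, fading in the IG or catch-up in the CG, and the planned data could not tell them apart.

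A second, smaller point concerns June itself. Release and post-test fall in the same month, and the article does not say which comes first for a given family.

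**Working it through.** **1. Timeline.**

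| Time | IG | CG |
|---|---|---|
| Baseline (Nov 2019 to Jan 2020) | measured | measured |
| Feb to May 2020 | six sessions, website, chat group | nothing |
| June 2020 | post-test | post-test; report and all materials (order not stated) |
| Nov 2020 | follow-up, questionnaire only | follow-up, questionnaire only (implied by Sections 2.2.3 and 2.2.8) |

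Only the June contrast compares the programme with no programme.

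**2. Reproducing the planned sample size.** Inputs from Section 2.2.3: f = 0.20, alpha 0.05, power 80%, g = 2 groups, m = 3 measurements, stated N = 42. Assumed, because the article gives neither: correlation between measurements r = 0.5 and sphericity (epsilon = 1). For the within-between interaction:

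- λ = f²·N·m/(1 − r) = 0.04 × 42 × 3/0.5 = 10.08
- df = (g − 1)(m − 1) = 2 and (N − g)(m − 1) = 80
- power = 0.803

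N = 42 is reproduced. With r = 0.3 the required N would be 58, and with r = 0.7 it would be 26.

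**3. Expressing f = 0.20 as a group difference.** Assume equal arms and an IG effect D (in SD units) that is fully sustained, so that the IG − CG differences are (0, D, D). Then f = D/√18, and D = 0.20 × √18 = 0.85 SD. The article states only f.

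**4. Letting the CG gain a share c of D by November.** The differences become (0, D, D(1 − c)).

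- Three-time interaction: f(c) = 0.20 × √(1 − c + c²), entered in the formula of step 2 with N = 42.
- Baseline-to-follow-up contrast: the SD of change is √(2(1 − r)) = 1. With 21 per arm the noncentrality is D(1 − c)/√(2/21), with 40 df and a two-sided t test at 0.05.

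| c | November difference (SD) | Power, baseline-to-follow-up | f(c) | Power, three-time interaction |
|---|---|---|---|---|
| 0 | 0.85 | 77% | 0.200 | 80% |
| 0.10 | 0.76 | 68% | 0.191 | 76% |
| 0.25 | 0.64 | 52% | 0.180 | 71% |
| 0.50 | 0.42 | 27% | 0.173 | 67% |
| 0.75 | 0.21 | 10% | 0.180 | 71% |

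A normal approximation gives values up to about 2 points higher in the third column.

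**5. Reading the table.** The loss falls mainly on the follow-up contrast. The interaction test never drops below 67% and recovers as c approaches 1, because a post-test effect that then disappears is itself an interaction. A significant interaction therefore says nothing about maintenance, and the two contrasts have to be read separately.

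**The case against.** Offering controls the materials after post-test is a deliberate and common courtesy, and the exposure is partial. The programme consists of six facilitated sessions, goal setting, logging and a chat group with reminders. Section 2.2.5 gives the CG materials, documents and a report, and mentions no sessions, facilitators or chat group. This stands. November still compares the full programme with late, passive access, and a difference that persists would be interpretable and probably conservative.

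A reader might infer that maintenance cannot be studied at all, or that the trial's main result is compromised. The documents do not support that. Only a reduced or null November difference is ambiguous. The June contrast is untouched by later release, and all accelerometry belongs to it.

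A reader might also take the power losses as a forecast. They are not: nothing in the article says how much CG families would gain, and the 0.85 SD effect, its persistence and r = 0.5 are assumptions.

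Two textual reservations also stand. Section 2.2.5 names both groups for baseline and post-test but names none for follow-up; that the CG is measured in November follows from Sections 2.2.3 and 2.2.8. And the order of post-test and release within June may be settled in the full protocol, so contamination of the post-test is a possibility to exclude, not something the article shows.

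What remains is that the release date, the follow-up date and the definition of the effect are all fixed in the article and do not fit together. No analysis can restore a November comparator without the materials.

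**Conclusion.** The concern holds for the November contrast and, in part, for the three-measurement interaction test. The likely direction of bias is toward zero, and its size is unknown. Under the stated assumptions, CG uptake of 10% to 50% of the effect would lower power for the baseline-to-follow-up contrast from 77% to between 68% and 27%, and for the interaction from 80% to between 76% and 67%. No stated figure is wrong on this account: N = 42 reproduces. The baseline-to-post-test comparison stands, provided that release follows each CG family's post-test. This should be fixed because the remedy is cheap and the affected contrast is part of the declared effect on the primary outcome, but it is not fatal.

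**What to change.** **Preferred.** State in Section 2.2.5 that each CG family receives its report and access to the materials only after completing the November 2020 measurement. This takes one sentence; the downside is that CG families wait about five months longer.

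**If the June release stands or has already happened** (the article carries web access dates of January 2021):

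- State that release follows completion of the CG post-test, or report the actual order.
- In Section 2.2.8, name the baseline-to-post-test group difference as the intervention-versus-control effect.
- Report the baseline-to-follow-up contrast separately. Keep the CG in it, and describe it as a comparison with a control group that has had the report and the materials.
- Add the point to the limitations in Section 4.

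Reporting follow-up only as change within the IG is not a good substitute. It gives up the concurrent control and confounds the June-to-November change with season and calendar time. The second route costs only text, but it leaves a reduced November difference ambiguous.

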#### 2.2.6. Procedure

The recruitment phase will take place in November 2019–January 2020. The CG will be asked to participate in a study that investigates health-related behaviors over time, whereas the IG will be asked to participate in a study providing six (inter)active father-child sessions over a total period of 14 weeks. When interested in participating, fathers will be able to register for the study by contacting the researcher (control group) or by registering through an online registration form available on the Run Daddy Run website (intervention group). After registration, the participants will be checked for their eligibility (see Section 2.2.2) and eligible fathers will be asked to complete an online questionnaire and to wear an accelerometer during 7 consecutive days (see Section 2.2.7). The baseline measurements will take place in November-December 2019 for the CG and in January 2019 for the IG. After the completion of the baseline measurements, participants of the IG will receive an email or text message in which they will be informed about the start of the intervention (i.e., date, time and location) and some practical information regarding the first session. In each session, attendance of the father-child dyads will be logged by the facilitators. When a father-child dyad does not attend a certain session, a message (i.e., text message or email) will be sent afterwards with a link to the website where both the information given in the information part and the exercises in the practical part can be found. However, participants who do not attend the first two sessions, will be excluded from the study. Last, post-test measurements will take place after the intervention, in June 2020 and the follow-up measurements will take place in November 2020.

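### Intervention families who do not attend the first two sessions are excluded after baseline, with no counterpart rule in the control group, which could tilt the effect towards the intervention

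*Protocol article*

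**What the plan says.** Section 2.2.6 (Procedure) sets the order of events: registration, eligibility check, baseline questionnaire and accelerometry, then the sessions. On the step from baseline to sessions it says "After the completion of the baseline measurements, participants of the IG will receive an email or text message" with details of the start. Facilitators log attendance at each session, and a dyad that misses one is sent a link to the material. The same section then adds that "participants who do not attend the first two sessions, will be excluded from the study".

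Only one group has sessions to miss. Section 2.2.6 says "The CG will be asked to participate in a study that investigates health-related behaviors over time". Fathers recruited for the IG are instead invited to the 14-week programme with its six sessions. No attendance or engagement condition is stated for the CG, and session attendance is not among the inclusion criteria in Section 2.2.2.

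Section 2.2.5 says that "participants will not be randomly assigned to the control group (CG) or intervention group (IG), but will be recruited subsequently". Section 2.2.8 defines the intervention effect as "the difference in pre-post-follow up evolution between control and intervention group", estimated by multilevel analysis with age and gender considered as confounders. On losses, Section 2.2.3 says: "Assuming an attrition rate of 20% [10], a total sample size of 51 fathers will be required".

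**The concern.** The rule selects one side of the comparison on behaviour seen after baseline. Families that enrol in the IG, complete baseline and then do not start are taken out, while nothing removes the less engaged families from the CG. The contrast in Section 2.2.8 then sets IG families that passed an engagement filter against all CG families.

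This is not a run-in. According to Table 4, sessions 1 and 2 are part of the programme. The excluded families may also be partly exposed, since the website is available for the full 14 weeks and missed material is sent out.

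Families are excluded from the study, not merely from the remaining sessions. On a plain reading their post-test and follow-up values would not exist, and a multilevel model could use their baseline value at most. The stated confounders do not capture engagement. What is at stake is the estimate for the primary outcome, and its relevance to wider roll-out, which the Discussion has in view and where early non-attenders would count.

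**Working it through.** **1. The plan's own figures.** For the repeated-measures group-by-time interaction, the noncentrality is f² × N × m / (1 − ρ), with f = 0.20, m = 3 measurements and k = 2 groups. Section 2.2.3 does not state ρ; 0.5 (with sphericity) is assumed here.
- N = 42: 0.04 × 42 × 3 / 0.5 = 10.08, with degrees of freedom (k − 1)(m − 1) = 2 and (N − k)(m − 1) = 80. Power is 0.803. N = 40 gives 0.782. So 42 reproduces.
- Attrition: 42 × 1.2 = 50.4, rounded up to 51. (42 / 0.8 = 52.5 would give 53; this point does not depend on the difference.)
- The allowance for losses is therefore 51 − 42 = 9 families over both groups and all causes.

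**2. When and where the rule acts.**

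| Step | IG | CG |
|---|---|---|
| Eligibility check and baseline | yes | yes |
| Sessions 1 and 2 | yes | none |
| Exclusion for non-attendance | possible | impossible |
| Post-test and follow-up | those not excluded | all enrolled |

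**3. Size of the bias.** The documents give neither the share excluded nor how much less such families change, so both are assumptions. Suppose the excluded share p is the lowest part of a normally distributed engagement score that correlates r with change. The mean change of the retained families then exceeds that of all IG families by r × φ(z_p) / (1 − p), in SD of change.
- p = 0.10: φ(−1.282) / 0.90 = 0.1755 / 0.90 = 0.195. With r = 0.3 the bias is 0.058; with r = 0.5 it is 0.097.
- p = 0.20: φ(−0.842) / 0.80 = 0.2800 / 0.80 = 0.350. With r = 0.3 the bias is 0.105; with r = 0.5 it is 0.175.

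The range is about 0.06-0.17 SD of change.

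**4. Second method.** If retained and excluded families differ by g SD in mean change, the bias is p × g.

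| Share excluded | g = 0 | g = 0.5 | g = 1.0 |
|---|---|---|---|
| 5% | 0 | 0.025 | 0.05 |
| 10% | 0 | 0.05 | 0.10 |
| 20% | 0 | 0.10 | 0.20 |

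Dividing each result in step 3 by its p shows that the correlations used there imply gaps of about 0.5-1.0 SD (for example 0.105 / 0.20 = 0.53 and 0.097 / 0.10 = 0.97), so the two methods agree.

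**5. Effect on false positives.** Assume about 25 families per group (51 / 2) and no true effect. The standard error of the difference is √(2/25) = 0.283 SD. By normal approximation, the two-sided 5% error becomes 5.4% at a bias of 0.05 SD, 6.4% at 0.10 SD and 10.9% at 0.20 SD. For 0.058 and 0.175 SD it is about 5.5% and 9.5%.

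**6. Effect on the attrition allowance.** With an IG of about 25, excluding 10-20% removes 2.5-5 families, that is 3-5 of the 9. With the three groups of about 12 dyads in Section 2.2.1 (36 dyads), it is 3.6-7.2, that is 4-7 of the 9.

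**The case against.** The strongest reply is that the study is openly quasi-experimental. The two groups are recruited one after the other, to differently described studies, so they already differ in motivation. No randomised comparison is broken, and CG families are not exchangeable with IG non-starters in any case. The rule is disclosed in advance and attendance is logged, so exclusions can be counted and reported. This stands, and it limits the severity. It does not remove the problem: a non-equivalent control design relies on comparable change over time, and filtering one group on engagement after baseline weakens that further.

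A reader might also infer several stronger things that the documents do not support.
- *The effect is certainly biased upward.* The documents do not say that early non-attenders change less. Illness or work can also keep families away, which would weaken the link with change; with equal change the bias is zero.
- *The exclusions use up the attrition allowance.* Step 6 shows that they take part of it.
- *The bias is a fixed percentage of the detectable effect.* The bias is in SD of change and f = 0.20 is on the SD of the outcome. These scales coincide only at a correlation of 0.5 between measurements, which Section 2.2.3 does not state.
- *Section 2.2.8 is at fault for naming no analysis set.* A condensed article may leave that to the analysis plan. The point rests on the stated rule.

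That the later data would not be collected is itself a reading of the exclusion, though the natural one; the article does not say expressly whether excluded families are still measured.

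**Conclusion.** The point holds as a should-fix. The text supports three facts: the exclusion follows enrolment and baseline, it depends on attendance, and it has no CG counterpart. The direction in favour of the intervention is conditional on early non-attenders improving less. The size is an illustration: about 0.06-0.17 SD of change if 10-20% of the IG is excluded and engagement correlates 0.3-0.5 with change, with the upper end needing both worst-case inputs, and zero if change is equal. The wording also leaves open whether a family must miss both sessions or either one, and this affects how many are removed. Missing both is the more natural reading and would remove fewer families.

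**What to change.** - Delete the exclusion from the evaluation. Invite every enrolled IG family with a baseline to the post-test and follow-up measurements, whatever their attendance.
- Make the primary analysis one of all families in the group they enrolled in.
- Use the existing attendance log for a secondary per-protocol analysis, and state there whether the criterion means missing both of the first two sessions or either one.
- If the rule has already been applied, report the number of families excluded and their baseline values.

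The cost is a change to one sentence of the protocol, questionnaires at both later visits and accelerometers at post-test for a few more families, and an estimate that may be less favourable. Some non-attenders will decline to be measured, but that is ordinary attrition, which can be reported, and not missing data created by the protocol.
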